### Setting

The ward at which the study is conducted initially has a total of 13 beds, with the possibility of adding 5 more; when rebuilt, there will be no possibility of adding extra beds. It is located in a building that was constructed in the late 1970s. Patients admitted, voluntarily or involuntarily, to the ward are 18 to 59 years of age and suffer from various types of mental ill-health that require specialist psychiatric treatment. The staff consists of registered nurses (RNs), mental health nurses (MHNs), and enrolled nurses. A ward manager, physicians, and a consultant psychiatrist also work on the ward, while other professions work as consultants to the ward. The ward door is locked. Certain rules and routines are followed in consideration of fixed times for medication, physicians’ rounds and other meetings, meals, smoking breaks, and walks outdoors. Medical treatment, i.e. medication, is the norm, while structured common activities, pre-planned dialogues, and other nursing interventions are sparse.

During the renovation period, the ward is relocated to an adjacent ward with the same structure as the original. Phase A, the first baseline measurements, takes place on this ward. Phase B is conducted on the rebuilt ward with the new spatial design.

### Participants

During phase A, phase B, and the follow-up, all patients admitted to the ward will be informed about the project by a research assistant. Furthermore, they will be invited to participate in the evaluation, which comprises completing questionnaires, using an activity monitor, and taking part in semi-structured interviews.

*Inclusion criteria for patients*: 18 years or older, admitted to the wards during phase A, phase B, and/or follow-up.

*Exclusion criteria for patients*: not fluent enough in Swedish to complete questionnaires and participate in interviews.

The research assistant will invite all staff working on the ward during phase A, phase B, and follow-up to participate in the evaluation.

*Inclusion criteria for staff*: regularly employed at the ward during phase A, phase B, and/or follow-up.

### Data collection

Data will be collected through questionnaires, activity measurements, ward registers, and semi-structured interviews.

#### Questionnaires

During both phases, measurements will be taken twice a week, with an assigned staff member distributing the questionnaires to the participants. Based on results from previous research [12, 34] showing that experiences of interactions with staff are related to experiences of the physical environment, the primary outcome measure for patients will be the perceived quality of their interaction with the staff. Secondary outcome measures will be levels of depressive symptoms, anxiety, satisfaction, and quality of care.

Based on results from previous research [13, 35, 36] showing that staff in psychiatric inpatient care experience stress related to inadequate physical environments, the primary outcome measure for staff will be perceived stress. Secondary outcome measures will be stress of conscience and quality of care. Demographic data will be collected for all participants.

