#### Patient-related questionnaires

The Caring Professional Scale (CPS) [37] will be used to measure the quality of patient–staff interactions. The CPS consists of 15 items answered on a 5-point Likert scale. Validity and reliability has been reported as satisfactory (Cronbach’s alpha nurses 0.97) [37].

The ultra-brief self-assessment scale, the Outcome Rating Scale (ORS) [38] will be used to measure satisfaction in three areas of client functioning, specifically individual, relational, and social functioning. The specific items measured on the ORS were adapted from the OQ-45.2 [39, 40]. The three areas are each assessed on a visual analogue scale, where the respondent places a hash mark on the corresponding 10 cm line, with low estimates to the left and high to the right. The ORS has adequate validity, solid reliability, and high feasibility [38].

The self-assessment scale the Hospital Anxiety and Depression Scale (HAD) [41] will be used to measure anxiety and depressive symptoms. All items are scored on a 4-point scale. The HAD appears to be a reliable and valid method for measuring emotional distress and has been shown to be sensitive to changes in response to psychosocial interventions [41, 42]. The Swedish version was tested and showed satisfactory validity and reliability (Cronbach’s alpha 0.90) [43].

The Quality in Psychiatric Care–Inpatient (QPC-IP) [44, 45] questionnaire will be used to measure quality of care. This instrument is part of the QPC family of instruments that originate from the QPC and contains 30 items that include important aspects of patients’ perceptions of quality of care. The QPC-IP is psychometrically adequate [45] and thus recommended for evaluating patients’ experiences of the quality of psychiatric care. The instrument measures six dimensions: encounter (8 items), participation (8 items), discharge (4 items), support (4 items), secluded environment (3 items), and secure environment (3 items), on a 4-point Likert-type scale, ranging from 1 (totally disagree) to 4 (totally agree), with the option of answering ‘not applicable’ on all items. The instrument also contains several background questions about demography and general clinical characteristics, and an open question inviting any other views on quality of care [44, 45].

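### A member of the staff being rated hands patients the form for the primary patient outcome, which may colour the ratings and affect who answers on each occasion

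*Protocol article*

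**What the plan says.** Under Questionnaires, the Protocol article has measurements taken in both phases "with an assigned staff member distributing the questionnaires to the participants". It then states that "the primary outcome measure for patients will be the perceived quality of their interaction with the staff". Patient-related questionnaires names the CPS as the instrument: "The CPS consists of 15 items answered on a 5-point Likert scale".

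Under Setting, the word staff is used for the people who work on the ward: "The staff consists of registered nurses (RNs), mental health nurses (MHNs), and enrolled nurses", together with a manager and physicians. The same section says "The ward door is locked", and "Patients admitted, voluntarily or involuntarily, to the ward are 18 to 59 years of age".

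Under Participants, a separate role appears: "all patients admitted to the ward will be informed about the project by a research assistant". That person also invites patients and staff to take part. The article gives this role no part in handing out forms.

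Under Analysis, Quantitative data, each point in the series is the average over whichever participants respond on that occasion. The numerical summary compares phase B points with the most extreme phase A value.

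**The concern.** The people whose conduct is being scored hand over the score sheet. The raters depend on them daily and some are detained. This is a procedure that the article states, so it cannot be put down to condensing a longer protocol.

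Two things could follow. First, patients may answer more kindly when staff handle the form. On a bounded scale this also leaves less room for improvement to show. Second, the distributor may affect which enrolled patients receive or complete a form on a given day, for example by not approaching someone who is distressed or dissatisfied. Staff know the phase and are study participants themselves. The Background also reports staff who wished for surroundings they could take pride in, so more goodwill towards the rebuilt ward is plausible.

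What is at stake is the A-to-B comparison of the primary patient outcome. With one ward and no comparison ward, a change in how forms are offered between phases would look the same as an effect of the design.

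**Working it through.** The article gives no CPS mean, SD, bias or response count, so there is no plan figure to reproduce. The check has a textual part and an illustrative part.

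**1. Who hands out what.** Distributor: a staff member (Questionnaires). Object of the rating: interaction with the staff (Questionnaires). Meaning of staff: ward personnel (Setting). The research assistant is named as a different role (Participants). Read together, the distributor belongs to the rated group. The text does not literally say ward staff, so this is the natural reading and not a certainty.

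**2. What cancels.** Let the observed ward mean be the true mean plus a bias b. The contrast is (true B + bB) − (true A + bA) = true change + (bB − bA). If bA = bB the bias drops out, except where scores reach the top of the scale. If the two differ, the difference goes straight into the result.

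**3. Leaving out one patient.** Suppose n patients would have answered and one lies 1 SD below the mean of the others. The full mean is the others' mean minus 1/n SD, so leaving that patient out raises it by 1/n SD.
- n = 5 (assumed): 1/5 = 0.20 SD
- n = 8 (assumed): 1/8 = 0.125 SD
- n = 13 (all regular beds, assumed enrolled and answering): 1/13 = 0.08 SD

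Direction matters. In phase B the omission favours the new design. In phase A it raises the reference value and makes improvement harder to show.

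**4. Simulation, with every value assumed.** Inputs: CPS item mean 3.5 in phase A, patient SD 0.8, scores clipped to 1–5, independent draws at each occasion, and 8 or 13 raters. Two schedules were used: 5 and 10 points (Table 1), and 10 and 8 points (Procedure: twice weekly for about 5 weeks, then weekly for about 2 months). PND, the percentage of non-overlapping data, is taken in its usual sense as the share of phase B points above the highest phase A point. With no change its expected value is 1/(nA + 1), that is 1/6 = 16.7% or 1/11 = 9.1%.

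Equal bias in both phases, true gain 0.4:

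| Bias | Gain seen (13 raters, 5/10) | Mean PND | Gain seen (8 raters, 10/8) | Mean PND |
|---|---|---|---|---|
| 0 | 0.375 | 70.3% | 0.380 | 44.9% |
| 0.5 | 0.334 | 68.5% | 0.334 | 44.4% |
| 1.0 | 0.258 | 65.1% | 0.256 | 40.6% |
| 1.5 | 0.162 | 58.9% | 0.162 | 35.3% |

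No true change, phase A bias 0.5, more bias in phase B (mean PND):

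| Schedule, raters | No bias in either phase | 0.2 more in B | 0.4 more in B |
|---|---|---|---|
| 5/10, 8 | 16.6% | 35.2% | 57.0% |
| 5/10, 13 | 16.6% | 40.8% | 68.8% |
| 10/8, 8 | 9.2% | 23.8% | 44.1% |
| 10/8, 13 | 9.5% | 28.9% | 57.8% |

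Equal bias has little effect on PND unless it is large. A modest difference between phases has a marked effect. These tables show which mechanism matters. They do not estimate what happens on this ward.

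**The case against.** The ward is its own control and the same distribution procedure is stated for both phases, so a steady courtesy effect mostly drops out. The equal-bias table supports this, and the point stands. What remains is bias or selection that differs by phase, and nothing in the article shows that it will occur. Staff would also know the phase whoever hands out forms, because the move to a rebuilt ward cannot be hidden.

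Return route, sealing and confidentiality wording are details that an article usually leaves to the full protocol. That is right, and their absence is not the criticism. Such safeguards, if they exist elsewhere, would reduce the problem but would not change the stated distributor.

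The Discussion acknowledges that the pragmatic approach, taken together with clinic management, leaves the evaluation less uniform than is customary. That lowers the weight of the point, but it does not mention this conflict of roles.

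A reader might infer that recruitment rates, a feasibility objective, are distorted too. The documents do not support that. The research assistant informs and invites patients, so enrolment does not pass through the distributor, and completion rates are not a listed objective. A reader might also assume that the research assistant is on hand at every round. The article does not say so.

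**Conclusion.** The concern holds as a risk created by a stated procedure. The primary patient outcome is a rating of staff, handed out by someone who is most naturally one of them, to patients in a dependent position. A stronger reading, that CPS scores are in fact inflated or pressed against the ceiling, is tempting but unsupported: the article gives no CPS level, distribution or evidence of a ceiling.

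The size cannot be derived. The only figures available are illustrations: a shift of 0.08 to 0.20 SD in a single ward mean if one patient 1 SD below the others is not approached, with 13 and 5 respondents assumed. The exposure that matters is a difference between phases in how favourably patients answer or in who is offered a form. The point affects the credibility of the patient comparison, not the recruitment findings, and no sample size figure changes. It merits correction because the remedy is cheap.

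**What to change.** If the research assistant is already present at measurement rounds, have that person distribute the patient forms (CPS, ORS, HAD, QPC-IP) in both phases.

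If not, keep staff distribution and add the following in both phases:
- a sealable envelope with each form, returned to a locked box that staff cannot open;
- a plain statement to patients that staff will not see their answers;
- the form offered to every enrolled patient present that day, with a log of offered, returned and refused.

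The envelope addresses courtesy bias. The log addresses selection by making it visible per occasion, and it is worth keeping under the first route as well. It would also help to separate a form that patients decline from one they were never offered, which bears on the objective about suitability for frequent measurement.

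If collection is already complete, report who distributed and collected the forms, state this as a limitation, and change the procedure in the later studies that the pilot is meant to inform.

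Cost: envelopes, a box, a tick-list and slightly more handling per round. The first route costs no extra staff time only if the research assistant already attends the rounds, which the article does not state.

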#### Patient-related questionnaires

The Caring Professional Scale (CPS) [37] will be used to measure the quality of patient–staff interactions. The CPS consists of 15 items answered on a 5-point Likert scale. Validity and reliability has been reported as satisfactory (Cronbach’s alpha nurses 0.97) [37].

The ultra-brief self-assessment scale, the Outcome Rating Scale (ORS) [38] will be used to measure satisfaction in three areas of client functioning, specifically individual, relational, and social functioning. The specific items measured on the ORS were adapted from the OQ-45.2 [39, 40]. The three areas are each assessed on a visual analogue scale, where the respondent places a hash mark on the corresponding 10 cm line, with low estimates to the left and high to the right. The ORS has adequate validity, solid reliability, and high feasibility [38].

The self-assessment scale the Hospital Anxiety and Depression Scale (HAD) [41] will be used to measure anxiety and depressive symptoms. All items are scored on a 4-point scale. The HAD appears to be a reliable and valid method for measuring emotional distress and has been shown to be sensitive to changes in response to psychosocial interventions [41, 42]. The Swedish version was tested and showed satisfactory validity and reliability (Cronbach’s alpha 0.90) [43].

The Quality in Psychiatric Care–Inpatient (QPC-IP) [44, 45] questionnaire will be used to measure quality of care. This instrument is part of the QPC family of instruments that originate from the QPC and contains 30 items that include important aspects of patients’ perceptions of quality of care. The QPC-IP is psychometrically adequate [45] and thus recommended for evaluating patients’ experiences of the quality of psychiatric care. The instrument measures six dimensions: encounter (8 items), participation (8 items), discharge (4 items), support (4 items), secluded environment (3 items), and secure environment (3 items), on a 4-point Likert-type scale, ranging from 1 (totally disagree) to 4 (totally agree), with the option of answering ‘not applicable’ on all items. The instrument also contains several background questions about demography and general clinical characteristics, and an open question inviting any other views on quality of care [44, 45].

#### Staff-related questionnaires

The Perceived Stress Scale (PSS) [46] will be used to measure stress among staff. The PSS consists of 10 items answered on a 5-point Likert scale. The Swedish version of the 10-item PSS has proved to have satisfactory validity and reliability (Cronbach’s alpha 0.84) [47].

The Stress of Conscience Questionnaire (SCQ) [48] will be used to measure the frequencies of stressful situations and the degree to which these lead to stress of conscience among staff. The SCQ consists of nine items with two parts each. The first part uses a 6-point scale ranging from never (0) to every day (5); in the second part, a 100 mm visual analogue scale ranging from ‘No, not at all’ (0) to ‘Yes, it gives me a very troubled conscience’ (5) is used for each of the nine items. Previous studies have reported satisfactory validity and reliability (Cronbach’s alpha 0.83 for the total SCQ) [49].

The Quality in Psychiatric Care–Inpatient Staff (QPC-IPS) [44, 45] questionnaire will be used to measure quality of care. This instrument is part of the QPC family of instruments that originate from the QPC [44, 45]. Psychometric tests have been performed internationally and are ongoing nationally. Results have yet to be published.

#### Activity measurement

Staff and patients will be invited to measure their free-living physical activity during their time spent on the ward during both phase A and phase B. ActivPAL (PAL Technologies, Glasgow in Scotland, UK) is a single-site instrument validated to quantify postural allocation during sedentary, upright, and ambulatory activities. The small, lightweight device is worn on the subject’s thigh for up to 1 week at a time. The device measures sedentary time, standing and stepping activities, and the intensity of a subject’s activities. The data is captured and analysed with custom designed software.

#### Data from ward registers

Data on the use of coercion and violent interactions, PRN medication, and length of hospital stays will be collected from the ward’s existing registers.

##### Semi-structured interviews

Both patients and staff will be interviewed by the researchers in semi-structured interviews [50]. Patients will be interviewed individually while staff will participate in focus groups. During phase B, patients will be interviewed very near to their discharge from the ward, while the focus group interviews with staff will be conducted at the end of phase B. The participants will be asked to share their experiences of the ward environment and its impact on the quality of their interactions. Staff will also be asked about the ward environment’s impact on their daily work and perceived stress. Table 1 shows a flowsheet of the data collection.

**Table 1 Tab1:** Modified SPIRIT-figure showing intervention and data collection flowsheet

Intervention phase	A					B									
Measurement no.	1	2	3	4	5	6	7	8	9	10	11	12	13	14	15
Assessments, patients															
CPS	●	●	●	●	●	●	●	●	●	●	●	●	●	●	●
ORS	●	●	●	●	●	●	●	●	●	●	●	●	●	●	●
HAD	●	●	●	●	●	●	●	●	●	●	●	●	●	●	●
QPC-IP	●														●
Interviews												●	●	●	●
Activity monitor		●	●							●	●				
Assessments, staff															
PSS	●	●	●	●	●	●	●	●	●	●	●	●	●	●	●
SCQ	●	●	●	●	●	●	●	●	●	●	●	●	●	●	●
QPC-IPS	●														●
Interviews												●	●	●	●
Activity monitor		●	●							●	●				
Observations at ward										●	●	●	●	●	●

*●*Measurement performed, *CPS* Caring Professional Scale, *ORS* Outcome Rating Scale, *HAD* Hospital Anxiety and Depression Scale, *QPC-IP* Quality in Psychiatric Care–Inpatient, *PSS* Perceived Stress Scale, *SCQ* Stress of Conscience Scale, *QPC-IPS* Quality in Psychiatric Care–Inpatient Staff, Supplementary data from ward registers will be collected continuously

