### Procedure

In the overall project, the evaluation will consist of two phases (A and B), and a follow-up, in line with the SSED. Baseline measures will be established during phase A, through outcomes measured twice a week for approximately 5 weeks. During these 5 weeks, staff and patients will not be introduced to the new environment. In phase B, staff and patients will be introduced to the new environment, and outcomes will be measured once a week over a period of 2 months.

The semi-structured focus group interviews with staff will be conducted at the end of phase B while patients will be interviewed individually very near to their discharge from the ward during phase B. Follow-up studies are planned for 6 and 12 months after phase B through interviews investigating whether the possible effects of changing the healthcare environment are sustainable [33].

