### Sample size

Sample size for the quantitative part is estimated at 25 staff members and 30 patients. For the qualitative part, sample size is estimated at 20 staff members and 20 patients who will be purposively selected by the researchers.

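### Table 1 places staff focus groups on stress inside the last four phase B measurements, so three or four of the ten phase B staff ratings may be subject to reactivity that has no phase A counterpart

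*Protocol article*

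**What the plan says.** All references are to the Protocol article.

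- **Outcome.** Under Questionnaires, "the primary outcome measure for staff will be perceived stress". It is measured with the PSS. SCQ and QPC-IPS are the secondary staff measures.
- **Content of the focus groups.** Under Semi-structured interviews, the topics put to staff include the environment's "impact on their daily work and perceived stress".
- **Timing in the text.** Under Procedure: "The semi-structured focus group interviews with staff will be conducted at the end of phase B". Semi-structured interviews says the same. Neither section says whether the groups come before, between or after the last questionnaires.
- **Timing in Table 1.** Phase A is measurements 1 to 5 and phase B is 6 to 15. Staff interviews are marked at 12, 13, 14 and 15 only. PSS and SCQ are marked at all 15 measurements. QPC-IPS is marked at 1 and 15.
- **Numbers.** Under Sample size, the questionnaires are planned for 25 staff and 30 patients. For the interviews and focus groups, "sample size is estimated at 20 staff members and 20 patients".
- **Analysis.** Under Quantitative data, each data point is the average over the staff who respond on that occasion. The phases are compared by visual inspection of level and trend and by a non-overlap percentage against the most extreme phase A point.

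**The concern.** The ward is its own control, so phase A and phase B ratings are comparable only if they are collected under the same conditions apart from the new design. A group conversation with researchers about whether the ward has changed staff stress is a difference in measurement conditions. It falls only in phase B, towards its end, and it concerns the same construct as the primary staff outcome. The ratings are self-reports by people who know which phase they are in. Such a conversation could move later ratings either way, through shared appraisal or through a sense of what answer is expected.

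Two things are at stake. A change in PSS or SCQ that begins only late in phase B would have two candidate explanations. And the first feasibility objective asks how well the questionnaires detect change, which is harder to answer if some of the late points may reflect the focus groups. QPC-IPS is the most exposed measure in one respect: it has a single phase B value, at the last measurement, and so no earlier phase B value to compare it with.

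**Working it through.** The plan gives no effect size, standard deviation or error rate for PSS, so there is no stated figure to reproduce and no power calculation applies. The check is a count from Table 1, followed by the weight of those points in the analysis.

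**1. Which points coincide.** Phase B has measurements 6 to 15, which is 10 points. Staff interviews are marked at 12, 13, 14 and 15, which is 4 points, and at 0 of the 5 phase A points.

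**2. Which ratings can follow a focus group.** Table 1 does not order activities within a measurement.
- Group before the questionnaire on each occasion: ratings at 12, 13, 14 and 15 can be affected, 4/10 = 40%.
- Group after the questionnaire on each occasion: a group at 12, 13 or 14 still precedes the ratings at 13, 14 and 15, so 3/10 = 30%.
- Neither case: ratings at 6 to 11, six points, all before the first marked group.

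**3. Weight in the non-overlap statistic.** Each phase B point carries 1/10 = 10 percentage points. The ceiling is therefore 3 × 10 = 30 or 4 × 10 = 40 percentage points. It is reached only if every one of those points changes its overlap status because of the discussion.

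**4. What the ceiling would look like (illustration).** Assume no true effect and exchangeable points. The chance that a phase B point lies beyond the most extreme of 5 baseline points in the favourable direction is 1/6, so the expected non-overlap is about 17%.
- Four late points all pushed beyond that extreme: (6 × 1/6 + 4)/10 = 50%.
- Three late points all pushed beyond it: (7 × 1/6 + 3)/10 = 41.7%.

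**5. Reach among raters.** Assume that all 20 focus-group staff are among the 25 questionnaire staff, which Sample size does not state, and that all 25 respond. Once all 20 have attended, 20/25 = 80% of raters have taken part. A change of d PSS points per attendee then moves the ward mean by 0.8d: 0.4 points for d = 0.5, and 2.4 points for d = 3. These values of d are assumptions, since the plan gives none.

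The 80% would build up if the sessions are spread out. With 5 staff per marked occasion (20/4, also an assumption), the share of raters who have already attended is:

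| Measurement | Group before questionnaire | Group after questionnaire |
|---|---|---|
| 12 | 5/25 = 20% | 0% |
| 13 | 10/25 = 40% | 5/25 = 20% |
| 14 | 15/25 = 60% | 10/25 = 40% |
| 15 | 20/25 = 80% | 15/25 = 60% |

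**6. After the change.** With all groups after measurement 15, 0 of 10 phase B points can follow a focus group. If points 12 to 15 are instead set aside in a sensitivity analysis, 6 phase B points remain against 5 baseline points.

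All counts are in Table 1 measurements. The calendar length of the window cannot be given, because Procedure and Questionnaires state different phase B measurement frequencies. Ward observations, also marked only in phase B (10 to 15), are not counted here.

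**The case against.** The best defence is that the focus groups are data collection for a process evaluation of the new design. Staff have not been introduced to that design in phase A, so a phase A counterpart would make little sense. Staff also answer stress questionnaires on every occasion in both phases and are prompted about stress throughout. Nothing in the article shows that a discussion shifts PSS. This stands, and it rules out calling the groups an extra intervention. It does not explain why they must overlap with outcome collection.

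A second defence is that the order is not given: a group may follow that occasion's questionnaires. This removes measurement 12 only. Groups at 12 to 14 come before the ratings at 13 to 15 whatever the order within an occasion. If the four marks are only a window, and every group was in fact held at 15 after the questionnaires, nothing would be affected. The text is compatible with that, but the table as drawn does not secure it.

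A reader might go further and infer that a late PSS effect cannot be separated from the focus groups at all. The documents do not support this. Six phase B points come before any marked group, so a change already present at 6 to 11 cannot come from them, and one that starts at 12 or 13 would visibly coincide with them. A reader might also extend the point to patients. That does not carry over well: patients are interviewed individually and shortly before they leave the ward, so few if any later ratings would follow.

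Finally, this is a small feasibility pilot that makes cautious claims. That stands, and it limits the severity.

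**Conclusion.** The point holds as a possible reactivity effect confined to the end of phase B. It concerns 3 of the 10 phase B PSS and SCQ points, or 4 if the group precedes the questionnaire at measurement 12. The single phase B QPC-IPS is also open to it if any group is held before that form is completed.

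The ceilings are 30 to 40 percentage points of non-overlap and 80% of raters. The first requires every exposed point to change status. The second requires the 20 interviewees to be among the 25 raters and all to have attended already. Neither is an expected value, and the article gives no size or direction for any shift. Measurements 6 to 11 remain usable as they are.

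This is an avoidable asymmetry between the phases, not a flaw that undoes the staff comparison. It is minor for a pilot, but worth correcting because the correction is cheap.

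**What to change.** In Procedure and in Semi-structured interviews, state that all staff focus groups are held after the last PSS, SCQ and QPC-IPS of phase B (measurement 15) have been returned. In Table 1, move the staff interview marks to a column after measurement 15.

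If that cannot be arranged, report PSS and SCQ level and non-overlap both with and without points 12 to 15, and record the date of each focus group against the questionnaire dates. This fallback does not help QPC-IPS, which has no other phase B value. For that measure, the order of group and questionnaire at 15 should at least be stated, together with whether any earlier group took place.

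The cost is a change of wording and one table edit, with the same interviews held somewhat later and no added data collection. Staff who leave just after phase B may be missed.
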